### Stress

This aspect will be assessed in the parents and their children using the Brazilian version of the Perceived Stress Scale [26], validated by Siqueira Reis et al. [27] which consists of 14 items about the frequency of feelings and thoughts related to events and situations that occurred in the last month, seven items being negative (1, 2, 3, 8, 11, 12 and 14) and seven items being positive (4, 5, 6, 7, 9, 10, and 13). Each item is answered on a five-point Likert frequency scale, with 0 = never and 4 = very often. The stress score is constructed by adding the values answered in each of the items, with positive items being on an inverse scale (0 = very often and 4 = never). The total score varies from 0 to 56 points and the higher the score, the higher the stress level.

### Comorbidities

Self-reported morbidities will be assessed by the following question: - Have you ever been diagnosed by a doctor or are currently taking medication for a health problem: ( ) Yes; ( ) No;

If the answer is positive, you will be asked which morbidity is in question among a series of morbidities (hypertension, diabetes, high cholesterol, triglycerides).

### Musculoskeletal symptoms

The presence of musculoskeletal symptoms will be assessed using a questionnaire developed by Kuorinka et al. [28]. This instrument assesses some musculoskeletal symptoms such as the presence of pain, tingling or numbness in different parts of the body (neck, shoulder, upper back, elbows, wrists/hands, lower back, hip/thigh, knees and ankles/feet). It is noteworthy that this instrument is also validated for use with children and adolescents [29]. The intensity of pain and how long the participant has felt pain will also be assessed on a scale of zero to ten.

### Lifestyle habits

#### Intensity of physical activity

The different intensities of physical activity will be measured objectively through the Actigraph GT3X accelerometer (ActiGraph, LLC, Pensacola, FL, USA), which is a light, portable, small, easy-to-use instrument designed to be positioned on the subject to record movements in the three orthogonal planes: vertical, horizontal anteroposterior and mediolateral. The accelerometers will be positioned laterally at waist height for those evaluated, who will remain with the equipment for four full days (three weekdays and at least one weekend day) [30]. Participants will be instructed to use the equipment throughout the day, removing it only when there is contact with water (taking a shower or swimming, for example) and during sleeping hours.

The ActiLife 6 program (ActiGraph, LLC, Pensacola, FL, USA) will be used to clean the data. Each data sample, determined by counts, will be summarized considering a specific time interval, this specific interval is designated as epoch, and lasts 60 s. The 60-second period was selected because it is the closest to the low-intensity, long-duration activity pattern [31]. Consecutive hours of zero counts and days with less than 10 h of monitoring will be excluded [32].

We will use the cutoff point recommended by Troiano et al. [30] to analyze the different intensities of physical activity. Light physical activity will be defined as 101–2019 counts per minute, moderate physical activity will be defined as counts between 2020 and 5998, vigorous physical activity will be defined as counts greater than ≥ 5999 cpm counts per minute. Activities below 100 counts per minute will be considered time in sedentary behavior.

Children and adolescents will be classified according to the cutoff points recommended by Evenson et al. [33], light physical activity will be considered 101–2295 counts per minute, moderate physical activity will be defined as 2296–4011 counts per minute and vigorous physical activity ≥ 4012 counts per minute. Activities below 100 counts per minute will be considered sedentary behavior.

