**Methods:**

The sample will consist of parents (father, mother, or both) and their children /adolescents. The participants will be recruited through public call by flyers spread across all the regions of the city and also through social media. The health parameters will include cardiovascular (cardiac autonomic modulation, blood pressure and resting heart rate), bone mineral density, anthropometric indices, handgrip strength, mental health (quality of life, anxiety and depression symptoms and stress), self-reported morbidities and musculoskeletal pain. Lifestyle habits will include physical activity levels, sedentary behavior, sleep parameters, eating patterns, smoking and alcohol consumption. Sociodemographic variables of age, sex, ethnicity and socioeconomic status will be considered as covariates. The follow-up visits of data collection will be scheduled after a period of 12 months from the baseline assessment during every twelve months.

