### Data collection

After sample recruitment has been carried out, data collection will begin. Graduate and undergraduate students will carry out data collection. Before data collection, all students will receive training for assessments in all procedures used in this study (questionnaires, accelerometers, heart rate monitors and DEXA).

Initially, participants will come to the São Paulo State University (UNESP). In this first evaluation, the interview will be carried out through the application of a questionnaire, in which the evaluators will collect data face to face with the participant. They will also carry out an assessment of blood pressure, resting heart rate and cardiac autonomic modulation through heart rate variability and at the end of this assessment the accelerometer will be given to the research participant with explanations and how this instrument should be used. Accelerometer collection procedures are described below:

(i) The individual will receive the accelerometer and one of the evaluators will explain how the device works (how to use and when to remove it) and will also leave a small manual with information about the device; (ii) Based on the cell phone number entered in the registration form of each subject who has the accelerometer, messages will be sent via SMS and/or WhatsApp reminding the study participant to use the accelerometer. If the subject only has a home telephone, the evaluator responsible for that subject will make a call reminding the subject to put on the device; (iii) On a pre-scheduled date, the participant will come to UNESP, deliver the accelerometer and carry out the final assessment, consisting of anthropometry (weight, height, waist circumference) and measurement of body composition using DEXA.

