#### Counfounders

Sociodemographic variables of age, sex, ethnicity and socioeconomic status will be considered as covariates.

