### Statistical analysis

The sample characterization variables will be expressed as mean and standard deviation if the data are parametric and median and interquartile range if they are not parametric. The association between lifestyle habits, as well as direct health measures carried out between parents and children, will be analyzed using Linear Regression adjusted by age of adolescents and their parents, socioeconomic status, parents’ education. In the case of using categorical analyses, Binary Logistic Regression or Poisson (with robust variance adjustment) will be used. The statistical significance to be used will be 5% and the confidence interval will be 95%. The statistical package used will be SPSS version 25.0.

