## Discussion

This research project will aim to verify the influence of parents’ health characteristics and lifestyle habits on their children. To this end, children and adolescents aged 6–17 and their parents will be assessed. Such information will be important, since lifestyle habits developed in childhood and adolescence tend to persist into adulthood [1, 3].

The family environment tends to guide the lifestyle habits of young people, and the current study will monitor participating families longitudinally. Among the important lifestyle habits to be monitored, we highlight physical activity. Christofaro et al. [16], in a study that evaluated the relationship between physical activity carried out by parents currently and also in the parents’ own childhood and adolescence, observed that the practice of physical activity among parents was positively associated with the practice of physical activity in their children.

In addition to the lifestyle habits between parents and their children we will also explore the possible role that physical activity in the associations. A main novelty will be to consider the possible role of physical activity in its different domains, analyzing occupational physical activity (work or housework for parents and physical activity at school for children), leisure-time sports and commuting actives. This project will also consider the role of different intensities of physical activity (light, moderate and vigorous) in the associations of lifestyle habits of parents and children.

Children, adolescents and active adults are less likely to be affected by cardiovascular diseases, for example, which are responsible for the highest causes of death in the world [20]. In the short term, this study could provide important information about the family environment in which health promotion strategies can be created. One of the answers we are aiming to obtain is if different types of physical activity and different types of intensity will have the same role between the associations of parents’ and children’s habits, or it will be different. With these estimates, for example, it will be possible to identify where health promotion actions should be prioritized for the population investigated.

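### The accelerometer models have no calendar term, so season or school holidays shared by parent and child could distort, though not by themselves produce, the planned parent-child association

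*Protocol article*

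**What the plan says.** All places are in the protocol article.

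- **Intensity of physical activity.** Participants "will remain with the equipment for four full days (three weekdays and at least one weekend day"). From this sample come light, moderate and vigorous activity and device-based sedentary time, for parents and children. Nothing links the days to school term or season.
- **Data collection.** The device is handed out at the first visit: "at the end of this assessment the accelerometer will be given to the research participant". It comes back later: "On a pre-scheduled date, the participant will come to UNESP, deliver the accelerometer". No calendar rule is attached to either date.
- **Statistical analysis.** The parent-child association is estimated by "Linear Regression adjusted by age of adolescents and their parents, socioeconomic status, parents’ education".
- **Confounders.** "Sociodemographic variables of age, sex, ethnicity and socioeconomic status will be considered as covariates".
- **Abstract, Methods.** "The follow-up visits of data collection will be scheduled after a period of 12 months from the baseline assessment", and yearly after that.
- **Physical activity performed in different domains.** A separate questionnaire (Baecke) scores activity at work or school, in leisure and in commuting over the preceding twelve months.

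**The concern.** Four days are a small sample of a person's usual activity, and what those days look like depends on when they fall. A weekday in the school holidays contains no school, and weather and daylight differ by season. Where parent and child are measured at about the same time, such a factor acts on exposure and outcome together. Omitted from the model, it adds to the parent-child correlation a part that has nothing to do with parental influence.

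The association between parents' and children's habits is the stated objective, and the separate role of each activity intensity is presented as part of the novelty. The intensities are measured by this device. The twelve-month spacing of visits keeps season roughly constant within a family across waves, but does not remove timing differences between families, and a parent-child association at any one wave is estimated between families.

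**Working it through.** **1. The plan's own figure.** Inputs from the Sample section: r = 0.31, power 80%, alpha 5% (taken as two-sided), +10% for loss, +20% for multiple regression.

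n = ((1.960 + 0.842)/atanh(0.31))² + 3 = (2.802/0.3205)² + 3 = 79.4, so 80 pairs or 160 people. 160 × 1.10 = 176; 176 × 1.20 = 211.2, so 212 people or 106 pairs. The stated 176 and 212 reproduce, and the point below does not affect them.

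**2. Significance threshold at 106 pairs.** tanh(1.96/√103) = 0.19.

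**3. Effect of a shared period.** The article gives no figure for timing, so two quantities are assumed: p, the share of families measured in a period (a holiday or a season) that shifts activity, and d, the size of that shift in SD, equal and in the same direction for parent and child. With unit variance within periods:

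- added variance and covariance: v = p(1 − p)d²
- induced r when the true r is 0: v/(1 + v)
- observed r when the true r is 0.31: (0.31 + v)/(1 + v)

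The last column is the probability of a significant result at 106 pairs when the true r is 0 (Fisher z, two-sided 5%).

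| p | d | v | Induced r | 0.31 appears as | P(significant), true r = 0 |
|---|---|---|---|---|---|
| 0.3 | 0.3 | 0.0189 | 0.02 | 0.32 | 5.4% |
| 0.3 | 0.5 | 0.0525 | 0.05 | 0.34 | 8.0% |
| 0.3 | 0.8 | 0.1344 | 0.12 | 0.39 | 23% |
| 0.5 | 0.3 | 0.0225 | 0.02 | 0.33 | 5.6% |
| 0.5 | 0.5 | 0.0625 | 0.06 | 0.35 | 9.2% |
| 0.5 | 0.8 | 0.1600 | 0.14 | 0.41 | 29% |

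A simulation with a shared factor explaining 5% and 10% of the variance in both members gave significant results in 8.3% and 16.7% of null studies; the formula gives 8.0% and 17.5%.

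**4. Opposite shifts.** If the period moves parent and child by equal amounts in opposite directions, the observed r is (0.31 − v)/(1 + v). For p = 0.3 and d = 0.5 this is 0.2575/1.0525 = 0.24: the association is masked rather than inflated.

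**5. Where the mechanism vanishes.** If nearly all families are measured in one season and in term, p(1 − p) goes to zero and so does v. If parent and child wear the device at different times of year, the shared part shrinks in the same way.

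**The case against.** The case against is substantial, and much of it stands.

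- **Timing is inferred.** The article does not say that families attend throughout the year. The Data collection section has collection starting after recruitment, and its length is not given, so it could be short. Nor does it say that parent and child wear the device in the same week; the procedure is described person by person. Both points stand, so the concern is conditional.
- **A condensed article may omit fieldwork scheduling.** This also stands: holidays may be avoided in practice. But the article does state covariates in two places. The two lists differ from each other (sex and ethnicity are only in one, parents' education only in the other), so neither need be final, yet neither includes timing.
- **Direction.** A school holiday need not change a parent's working week, so an equal shift in both members is a simplification. Upward bias is the usual result of shared timing, not a certain one.
- **Scope.** The Baecke scores cover twelve months and hardly depend on the week of attendance. The Discussion's reference to "physical activity at school for children" concerns those questionnaire domains and lends no support here.

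A reader might infer that the calendar alone could create the association the study is looking for. The figures do not support that: no scenario above induces an r that reaches 0.31, or even the 0.19 threshold. What the induced r can do is raise the chance that a null association crosses that threshold, and this is marked only at the assumed shift of 0.8 SD.

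**Conclusion.** The point holds as a conditional and limited one. For accelerometer-based intensity and sedentary time, the stated design controls only the weekday/weekend mix and the stated models have no calendar term. If collection crosses seasons or holidays and family members are measured at about the same time, the parent-child association can be biased, usually upward. Under the assumed ranges (p of 0.3 to 0.5, d of 0.3 to 0.8 SD, equal and same-direction shifts) the induced r is about 0.02 to 0.14, and a true 0.31 would appear as about 0.32 to 0.41. At shifts of 0.5 SD or less the distortion is at most about 0.04 on a true 0.31, small beside a sampling error of roughly 1/√103 = 0.10 on the Fisher z scale. None of these inputs comes from the article, so the true size is unknown. This is a cheap improvement to the analysis; it does not show that the design is unsound.

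**What to change.** In Statistical analysis, for models that use accelerometer measures, add calendar period of wear as covariates: quarter of the year, plus an indicator for school term or holiday, both from the recorded wear dates. If parent and child were measured in different periods, code the terms from the child's dates, since the child's activity is the outcome.

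The cost is 3 degrees of freedom for quarter and 1 for the indicator, 4 in all against 106 pairs, plus a look-up of the school calendar. If all wear falls in one quarter and in term, the terms drop out and nothing is lost.

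Restricting wear to school term is optional: it would narrow the target to term-time behaviour and slow fieldwork. A rule keeping reassessments in the baseline quarter would add little to the twelve-month interval already planned.

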### Physical activity performed in different domains

Physical activity in different domains will be assessed using the questionnaire by Baecke et al. [34], validated for adults [35] and young Brazilians [36]. Baecke’s questionnaire consists of 16 questions in which the last twelve months are considered, evaluating occupational physical activities (work in the case of adults) and at school (in the case of children and adolescents), sports practice and/or systematized exercises in the leisure and active commuting. In the work (or school) domain, issues relating to physical efforts carried out at work (or school) are investigated, such as: time spent sitting, standing and walking in the work environment (or school), carrying weights, whether the subject being assessed sweats a lot in the workplace (or school), work and how tired you feel after a day of work (or school). In the leisure domain, leisure-time physical activity is considered, such as exercising at the gym or playing sports. In this domain, the intensity of the physical effort of these activities (light, moderate, vigorous), the number of hours per week in which these activities are practiced and how long this physical activity has been practiced (< 1 month, 1–3 months, 4–6 months, 7–9 months, > 9 months) will be evaluated. In the field of active commuting, different physical activities are considered for this purpose, especially considering the amount of time spent walking to the mall, market or work. The time spent cycling is also considered.

In the end, this instrument offers a dimensionless score for each of the domains and the sum of the scores for the three domains also determines the total amount of physical activity practiced by each of the individuals evaluated.

### Sedentary behavior

To assess sedentary behavior, participants (parents and children) will answer the Sedentary Behavior Questionnaire [37]. It includes the domains of sedentary behavior (watching TV, playing video games and computer, sitting listening to music, sitting talking or typing on the mobile phone, working on the computer or bureaucratic tasks {e.g. answering emails}, playing a musical instrument, doing construction work art or crafts, sitting in a car, bus, or train) during the week and on weekends. The time spent using social media (Instagram, WhatsApp, Twitter, Facebook, etc.) will also be taken into account.

### Sleep quality

The Mini-sleep Questionnaire [38] will be used in the present study to evaluate the quality of sleep of parents and their children. This instrument is validated for the Portuguese language [39] and has 10 questions with seven possible answer options (never = 1, very rarely = 2, rarely = 3, sometimes = 4, often = 5, very often = 6 and always = 7) and provides a dimensionless score (higher score, worse sleep quality). The score for this instrument ranges from 0 to 70, with worse sleep quality being identified in higher scores.

The amount of hours of sleep will be assessed by the number of hours slept by the participant on a typical night.

### Eating habits

Eating habits will be verified through the frequency of weekly consumption of different foods based on the work of Block et al. [40]. The consumption of foods such as vegetables, fruits, cereals, dairy products, fried foods, sodium and sugary drinks (soft drinks), as well as stimulant (energy) and caffeinated drinks will be analyzed. They will be characterized by high consumption of these subject foods with consumption equal to or greater than five times a week. Individuals who are classified as consuming vegetables, fruits, cereals and dairy products with a weekly frequency of less than five times a week and/or are classified as having an intake of sodium, fried foods and sugary drinks more frequently than five times a week will be classified as having inadequate food.

### Smoking and alcohol consumption

Smoking will be assessed using the following question: Do you smoke, have you smoked, or have you never smoked? If you smoke, how many cigarettes do you usually smoke per day, considering the last month? If you have smoked, how long have you smoked and how long have you stopped smoking?”

Exposure to tobacco among non-smokers and ex-smokers will be assessed by the following question: “Do you have close contact with any smokers? Yes or no?”

Alcohol consumption will be assessed by the weekly frequency of alcohol intake and the number of doses consumed. Adults who reported drinking alcoholic beverages with a frequency equal to or greater than 1–2 days a week with an intake of 1–2 drinks per day will be considered to have high alcohol consumption (each dose will correspond to 250 ml for beer and 40 ml for distilled beverages).

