## Methods

The present study entitled the EPI-Family Health Study.

This study is an initiative to monitor different health parameters in the family environment. We will assess autonomic and cardiovascular systems (cardiac autonomic modulation, blood pressure and resting heart rate), bone mineral density, anthropometric indices, handgrip strength, mental health (quality of life, anxiety and depression symptoms and stress), self-reported morbidities and musculoskeletal pain outcomes. Lifestyle habits will include physical activity levels, sedentary behavior, sleep quality and time, eating patterns, smoking and alcohol consumption.

The invitation to participate in the study will be made through different means (social media, posters, folders, researchers going to schools). At the end of the evaluations, a didactic feedback will be prepared with the main results and a doubt channel will be made available where participants can be guided. This study will have a longitudinal design and the objective is for reassessments to take place annually. It is noteworthy that the present study is supported by the São Paulo Research Foundation (FAPESP; process: 2022/16437-8).

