### Sample

The sample for this longitudinal study will consist of adults and children and adolescents aged 6–17 years. The study will be carried out in the city of Presidente Prudente, located in the southeast region of Brazil and which has approximately 230,000 inhabitants according to information from the Brazilian Institute of Geography and Statistics.

Sample recruitment will take place through flyers spread across the five regions of the city (north, south, east, west and central area) and also through social media (Facebook, Instagram, Whatsapp, radio, TV) and researchers going to schools to extend the invitation. The inclusion criteria will be considered: i) children, adolescents and parents who do not have a pacemaker (as it can influence the results of the assessment of cardiac autonomic modulation, ii) who carry out all the assessments proposed by the study; iii) who have not used any type of caffeinated or alcoholic beverage in a period of 12 h before the assessments.

To calculate the sample, a correlation of 0.31 was used based on the study by Christofaro et al. [15] for the relationship between the physical activity of parents and children, considering a power of 80% and an alpha error of 5%. Anticipating possible sample loss, an additional 10% will be added to this calculation, totaling a minimum number of 176 participants. However, as multiple regressions will be carried out in the present study, the sample size was increased by 20%, totaling a final sample number of 212 participants to be evaluated (106 children and/or adolescents and at least one of their parents to be evaluated). The intention of the present study is to carry out reassessments every twelve months.

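### The adult category of high alcohol consumption has no single lower bound and no open upper end on drinks, so any analysis that uses it risks misclassification or pooling of very different intakes

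*Protocol article*

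**What the plan says.** The section Smoking and alcohol consumption first says what is collected: "Alcohol consumption will be assessed by the weekly frequency of alcohol intake and the number of doses consumed". That sentence is not restricted to adults. The section then defines a category of high consumption for adults only, by a frequency "equal to or greater than 1–2 days a week with an intake of 1–2 drinks per day". The first limb of this rule concerns days and the second concerns quantity. The dose is fixed by volume: "each dose will correspond to 250 ml for beer and 40 ml for distilled beverages".

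Alcohol is one of the lifestyle habits listed in Methods ("sleep quality and time, eating patterns, smoking and alcohol consumption"). The Statistical analysis section relates habits between parents and children by adjusted linear regression, and provides for binary logistic regression or Poisson regression with robust variance where categorical analyses are used. It does not say which form the alcohol variable will take.

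**The concern.** The article does not leave the definition open for a later document. It states a rule, with dose volumes, and an analyst would be entitled to code it as published. Two features of the wording prevent that from being done in only one way. Each limb is given as a range of one to two rather than as a number, and the phrase that opens the limb upwards is attached to days but not to drinks.

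If the binary enters a logistic or Poisson model, two analysts with the same data could place the same parent in different groups. On the literal wording, adults who take three or more drinks on a drinking day would join abstainers in the not-high group. On the more generous wording, they would share a group with adults who take one drink a week. In both cases the word *high* would tell a reader little about intake.

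**Working it through.** The plan gives no calculated figure on this point, so there is none to reproduce. The check applies the rule, as worded, to simple drinking patterns.

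**Inputs** (all from Smoking and alcohol consumption): days limb, at least 1–2 days a week; drinks limb, 1–2 drinks per day; one dose = 250 ml of beer or 40 ml of spirits. I take a drink and a dose to be the same unit, and the dose count to be per drinking day.

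**Formula:** doses per week = drinking days per week x doses per drinking day.

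**Step 1: the lower bound.** Each limb can be read as starting at 1 or at 2.

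- 1 day x 1 dose = 1 dose a week (250 ml of beer)
- 1 x 2 or 2 x 1 = 2 doses (500 ml)
- 2 x 2 = 4 doses (1000 ml)

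The entry point thus varies fourfold. If the drinks limb is kept as a closed range, one drink already satisfies it, and only the days limb is uncertain (1 or 2 doses a week). The value of 4 arises when both limbs are minima starting at 2.

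**Step 2: who is in the class.** The literal reading is at least 1 day and 1 to 2 drinks. The minimum reading is at least 1 day and at least 1 drink.

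| Days per week | Drinks per drinking day | Doses per week | Literal | Minimum |
|---|---|---|---|---|
| 1 | 1 | 1 | high | high |
| 1 | 3 | 3 | not high | high |
| 2 | 2 | 4 | high | high |
| 7 | 2 | 14 | high | high |
| 7 | 3 | 21 | not high | high |

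On the literal reading the class is not ordered by intake: 1 and 14 doses a week are in, while 3 and 21 are out. No pattern with three or more drinks on a drinking day qualifies, whatever the number of days.

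On the minimum reading the ordering problem disappears. But anyone who drinks on at least one day a week will ordinarily take at least one drink on that day, so the class is close to drinking at least weekly and holds 1 and 21 doses together.

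**Step 3: the stricter minimum reading.** With at least 2 days and at least 2 drinks, 2 x 2 = 4 doses is high, but 1 day x 6 drinks = 6 doses is not, because the days limb fails. Adding 'or more' without choosing the bounds therefore does not settle the class.

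**The case against.** The strongest reply is that the intention is plain enough. A class called high is unlikely to be meant to drop those who drink more, and the words about equalling or exceeding can be taken to govern days and drinks together. The ranges may also be response bands in the questionnaire, so that the rule is one cut at the lowest of these bands. Both are plausible, but the article neither prints the response options nor says that the drinks limb is a minimum. If both are granted, the result is the minimum reading starting at one day and one drink, which is where *high* comes close to any weekly drinking. The inversion is then answered, but not the fit between label and class.

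The reply is right on the use of the rule. A reader might infer that the parent-child alcohol association cannot be analysed validly. The documents do not support that: frequency and doses are both collected, Statistical analysis names linear regression first, and nothing there requires the category.

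A reader might also infer that there is no alcohol variable for the children. The collection sentence is not limited to adults. Leaving an adult label off participants aged 6–17 is no error, and how a child variable is derived is detail that an article may leave to the full protocol or analysis plan.

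Nor is attenuation demonstrated. The documents give no distribution of intake, the two readings misclassify different people, and the spread of doses within a class does not measure bias. Whether light weekly drinking deserves the word *high* on health grounds is also not at issue, since the documents give no standard to judge it by.

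**Conclusion.** The point stands in a narrow form: the adult category is stated, but badly fixed. Its lowest qualifying intake is 1 to 4 doses a week depending on the reading. Followed literally, it leaves out every pattern of three or more drinks per drinking day. Followed generously from one day and one drink, it nearly equals drinking at least weekly. Any logistic or Poisson analysis that uses it risks misclassifying or pooling very different intakes. The size and direction of a resulting bias cannot be given from the documents.

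This rests on the published wording and on taking drinks and doses as the same unit. It concerns one of several listed habits. The sample size calculation rests on physical activity and is not affected.

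**What to change.** Derive doses per week as days per week times doses per drinking day, and analyse it as a continuous or ordered variable. If a binary is kept for categorical analyses, rewrite it as one unambiguous lower bound with 'or more', chosen by the investigators before analysis, and give it a label that matches what the bound includes. Where doses per week is used, confirm that the dose question refers to a drinking day.

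The cost is a change of wording; both quantities are already collected, so no new adult data are needed. The drawback is a slightly less direct comparison with any earlier work that used the binary.
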